#### **8.4 Withdrawal of individual subjects**

Patients who decide to withdraw from treatment will continue to participate in follow-up assessments, unless they withdraw from the study completely. Subjects can leave the study at any time for any reason if they wish to do so without any consequences. The investigator can decide to withdraw a subject from the study for urgent medical reasons.

##### **8.4.1 Specific criteria for withdrawal (if applicable)**

Not applicable.

#### **8.5 Replacement of individual subjects after withdrawal**

Subjects who withdraw from the study will not be replaced.

#### **8.6 Follow-up of subjects withdrawn from treatment**

Patients who withdraw from treatment can agree to participate in follow-up.

#### **8.7 Premature termination of the study**

If the Sponsor, the Investigator(s), or Regulatory Authorities discover any condition during the study that indicate that the study or study site should be terminated, this action may be taken after appropriate consultation between the Sponsor and the Investigator(s). The Sponsor has the right to terminate the participation of either an individual site or the complete study at any time. This action may be taken based on the recommendation of the independent DSMB.

Reasons for termination may include, but are not limited to, the following:

- The incidence and severity of AEs in this or other studies indicates a potential health hazard to subjects;
- Subject enrolment is unsatisfactory;

- Data recording is inaccurate or incomplete to an unacceptable extent;
- Investigator(s) do not adhere to the protocol or applicable regulatory guidelines in conducting this study;
- Submission of knowingly false information from the study site to the Sponsor or regulatory authorities;
- Results of an interim analysis supporting terminating the study.

In the event that the study is terminated early, the Sponsor will provide specific guidance to investigational sites regarding the end-of-study procedures.

## **9. SAFETY REPORTING**

### **9.1 Temporary halt for reasons of subject safety**

In accordance to section 10, subsection 4, of the WMO, the sponsor will suspend the study if there is sufficient ground that continuation of the study will jeopardize subject health or safety. The sponsor will notify the accredited METC without undue delay of a temporary halt including the reason for such an action. The study will be suspended pending a further positive decision by the accredited METC. The investigator will take care that all subjects are kept informed.

### **9.2 AEs, SAEs and SUSARs**

#### **9.2.1 Adverse events (AEs)**

Adverse events are defined as any undesirable experience occurring to a subject during the study, whether or not considered related to cTBS treatment. All (serious) adverse events reported spontaneously by the subject or observed by the investigator or his staff during a 3-week period after the start of the first cTBS treatment will be recorded. Reporting is limited to a 3-week period because the side effects of rTMS are limited to 24 hours after stimulation. Additionally, stroke survivors have an increased risk of developing secondary medical conditions that are unrelated to cTBS treatment. During the follow-up period, in which only motor function tests and questionnaires are acquired AEs and SAEs will not be reported.

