#### **8.1.2 Secondary study parameters/endpoints**

A detailed description of secondary outcomes and assessments are provided in section 8.3.

Secondary endpoints are the FM-UE at 12 months post-stroke and the Action Research Arm Test (ARAT), nine hole peg test (NHPT), modified Rankin scale (mRS), hand and participation sections of the stroke impact scale (SIS), Barthel Index and the EuroQol - 5 dimensions – 5 levels (EQ-5D-5L) at 90 days and 12 months post-stroke.

An additional secondary outcome is the change in contralesional corticospinal excitability during the course of treatment. Therefore, the contralesional RMT is measured prior to each cTBS session (these data are already acquired to determine stimulation intensity). Contralesional inhibition is assessed to determine whether cTBS treatment had a direct inhibitory effect. This is done for cTBS session 1, 6 and 10 by acquiring the average MEP amplitude for 10 TMS pulses delivered to the contralesional M1 at 110%RMT.

Furthermore, a secondary outcome is the ipsilesional corticospinal excitability directly after the final cTBS session. Therefore, the ipsilesional RMT is measured before the first and after the final cTBS session.

TMS disruption will be assessed at baseline to determine whether contralesional M1 activity is maladaptive for affected hand performance, as this may predict cTBS treatment outcome. This will only be performed at De Hoogstraat Rehabilitation.

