## 8.3 Study procedures

A local investigator will perform screening and the informed consent procedure described in section 11.1. After written informed consent is obtained, baseline assessments will be performed. Baseline assessment duration is up to 90 minutes. Descriptions of the study procedures to determine the outcome measures (Table 1) are provided below.

After the baseline assessments, patients undergo the intervention described in section 5.1. The following data related to cTBS treatment is acquired: date and time of each treatment, the resting motor threshold, experienced side-effects and the number of minutes of upper limb therapy after the previous session. At the end of treatment course, the following data is acquired: the number of completed treatments,

the duration of the treatment course in days, and whether the patient thinks he/she received active or sham treatment.

At 90 days and 12 months post-stroke, the outcome measures described in table 1 are reassessed. Follow-up assessment duration is up to 90 minutes per follow-up. Detailed descriptions of these tests are provided below.

After the patient has been discharged, the total amount of upper limb therapy received during clinical rehabilitation and the length of stay at the rehabilitation center are acquired.

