### **Contralesional inhibition (optional)**

Contralesional inhibition is determined based on the ratio between the average MEP amplitude in response to 10 stimuli at 110% RMT before and after cTBS sessions 1, 6, and 10. The stimulation location is the motor hotspot, as identified prior to cTBS

treatment (to determine the cTBS treatment location). The RMT is also determined before the 1st, 6th and 10th cTBS treatment (to determine cTBS stimulation intensity).

TMS disruption (optional)

TMS disruption consists of a train of 30 active or sham TMS pulses at 10Hz and 90% RMT, delivered over the contralesional M1. The participant is instructed to start tapping the index finger of the affected hand at the onset of an auditory stimulus at 0s for a duration of 3 seconds at maximum frequency. The train of TMS pulses covers the entire finger tapping period. Finger tapping frequency is recorded using a key on a keyboard with the wrist fixed to the table using a velcro strap to minimize variability in task execution. 5 sessions of sham and 5 sessions of active TMS interference of the contralesional M1 are acquired.

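### Adverse event recording opens at the first cTBS session, so non-serious harm from optional study TMS given before it has no recording rule, and the rules for serious harm conflict

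*Combined protocol and SAP*

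**What the plan says.** Protocol section 9.2.1 defines an adverse event broadly, as "any undesirable experience occurring to a subject during the study, whether or not considered related to cTBS treatment". It then narrows what is written down: events, explicitly including serious ones, that the subject reports or staff observe "during a 3-week period after the start of the first cTBS treatment will be recorded". The reason given is that "the side effects of rTMS are limited to 24 hours after stimulation".

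Two study-specific TMS procedures are placed at baseline.

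- **TMS disruption.** Section 8.1.2 states: "TMS disruption will be assessed at baseline to determine whether contralesional M1 activity is maladaptive for affected hand performance". It restricts the test to one centre, and section 8.3 marks it optional. Section 8.3 describes the stimulation: "TMS disruption consists of a train of 30 active or sham TMS pulses at 10Hz and 90% RMT, delivered over the contralesional M1". On quantity it says: "5 sessions of sham and 5 sessions of active TMS interference of the contralesional M1 are acquired".
- **Ipsilesional resting motor threshold (RMT).** Section 8.3 marks it optional and places it at baseline and after session 10. Table 1 of section 3 says before the first session.

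On the order of events, section 8.3 says: "After the baseline assessments, patients undergo the intervention described in section 5.1". The same section lists experienced side effects among the data acquired in relation to cTBS treatment. It has no matching item for baseline TMS. SAP section 7.8 tabulates adverse events and serious adverse events by treatment group and says nothing about events before the first session.

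**The concern.** The recording window is tied to the treatment, whereas the exposure that could cause harm is stimulation of any kind. The disruption trains are repetitive stimulation, given for research purposes to patients within three weeks of a stroke. They are delivered at a higher intensity relative to threshold than the treatment itself. The risk figures in protocol sections 6.4, 11.4 and 13.1 concern theta burst stimulation, and none addresses 10 Hz trains at 90% RMT.

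A site that follows section 9.2.1 to the letter would not record a headache after the disruption test that cleared before session 1. For a serious event, the site would find one section that excludes it and others that appear to require it. The tabulated events, and the adverse event data that the DSMB sees under sections 9.5 and 10.5, would then be incomplete for a procedure that the study itself introduced.

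**Working it through.** The documents state no figure to reproduce for this point. The check compares timing and recording rules, with some arithmetic on exposure.

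**1. Exposure before the window (protocol sections 8.3 and 5.1)**

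- Train length: 30 pulses / 10 Hz = 3.0 s, which agrees with the stated 3-second tapping period.
- Active disruption pulses: 5 trains × 30 = 150, at 90% RMT.
- One cTBS session: 3 pulses × 5 bursts per second × 40 s = 600, which agrees with the stated 600, at 70% RMT.
- Relative intensity: 90/70 = 1.29.
- Relative quantity: 150 / (10 × 600) = 2.5% of the pulses in a full course.

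The baseline exposure is therefore small in number of pulses and higher in intensity relative to threshold.

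**2. The protocol's own rationale**

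Section 9.2.1 justifies the window by a 24-hour limit on rTMS side effects. Applied to the disruption test, that reasoning calls for recording from the test onwards. If the test is done more than 24 hours before session 1, its effects would, on the protocol's own premise, be over before recording opens. The interval between baseline TMS and session 1 is not stated.

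**3. Which rule would capture an event that starts and resolves before session 1?**

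| Provision | Non-serious event | Serious event |
|---|---|---|
| 9.2.1, recording window | Not captured | Not captured, as the window expressly covers serious events too |
| 8.3, side-effect item | Not captured; tied to cTBS treatment | Not captured, for the same reason |
| 9.2.2, SAE reporting | Not applicable | Apparently captured; no start date. Expected SAEs go to the eCRF within 7 days without expedited reporting |
| 9.2.3, SADE reporting within 24 hours | Not applicable | Captured only if not in agreement with the device's instructions for use; no start date |
| 9.4, follow-up | Follows events but sets no start of recording | Requires reporting to end of study; no start date |

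The non-serious column has no capturing entry. The serious column contradicts itself. Epileptic seizure is on the event list that precedes Appendix C, read here as the Appendix B list of expected SAEs. On that reading a seizure would be documented in the eCRF but exempt from expedited reporting.

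**4. Number of patients**

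- TMS disruption: 454 patients / 16 centres (SAP section 2) = 28.4, so about 28. This assumes equal recruitment and that every patient at the one centre is tested. Lower uptake reduces it. If that centre recruited twice the average, the figure would be 2 × 454/16 = about 57.
- Ipsilesional RMT: no uptake figure is given, so no count can be derived.
- Contralesional RMT before session 1: not counted. Section 8.3 describes it as part of the treatment procedure, and section 2.2 of the health-economic plan includes target localisation and dose determination in a cTBS session.

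The documents give no event rate for the 10 Hz trains, so no expected number of missed events can be calculated.

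**The case against.** The strongest reply is that the gap may be nearly empty in practice. The disruption test needs a contralesional RMT, and the only one described belongs to the session procedure. The documents also use baseline loosely: the ipsilesional RMT is at baseline in section 8.3 and before the first session in Table 1. The test may therefore take place at the session 1 visit, minutes before treatment or even after the session has formally begun. Events that start or persist after the window opens would then be recorded. This is a fair reading, but the text does not fix it. Section 8.3 puts baseline assessments before the intervention, and nothing ties the test to the day of session 1.

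Three stronger inferences are tempting, and the documents do not support them.

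- A reader might infer that all 454 patients are exposed before recording starts, because everyone has an RMT before session 1. The contralesional RMT is described as part of the treatment session, so it is not clearly outside the window.
- A reader might infer that no serious event before session 1 would ever be captured. Sections 9.2.2, 9.2.3 and 9.4 have no start date and can be read as requiring it. The accurate statement is that the sections conflict.
- A reader might infer that a patient harmed at baseline who never starts cTBS disappears from the trial. A randomised patient of this kind leaves the primary population (SAP section 6.1) but remains in the ITT2 sensitivity analysis (7.6) and in the flow diagram with reasons for withdrawal (7.1). If the event precedes randomisation, no intention-to-treat population is affected. The documents do not say whether randomisation comes before baseline TMS.

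It also stands that the test is specified identically for both arms, so the gap gives no reason to expect bias in the active-versus-sham safety comparison.

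**Conclusion.** The concern holds in a limited form. Non-serious events caused by the optional TMS disruption test or the optional baseline ipsilesional RMT have no recording rule if they resolve before session 1. For serious events in the same period, section 9.2.1 conflicts with 9.2.2, 9.2.3 and 9.4.

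The size is modest: about 28 patients for the disruption test under the assumptions stated above, each receiving 150 active pulses at 90% RMT, plus an unknown number with the ipsilesional measurement. The conclusion also assumes that these procedures are done before the first session starts, as section 8.3 implies. If they fall within the session 1 visit, the gap shrinks to the time between them and the start of that session. The effect is on the completeness of the safety record for study procedures. The efficacy analysis and the randomised safety comparison are unaffected.

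**What to change.** 1. In protocol section 9.2.1, start AE and SAE recording at the first study TMS pulse of any kind, whether threshold determination or TMS disruption.
2. In section 8.3, extend the side-effect item to the baseline TMS procedures, and record their date and time so that the interval to session 1 is known.
3. In SAP section 7.8, list events between the first study TMS pulse and the first cTBS session separately, including patients who never start cTBS. A separate listing also accommodates anyone not yet randomised.
4. Reconcile the recording period in 9.2.1 with 9.2.2, 9.2.3 and 9.4, so that all four state the same start and end for serious events. Changing 9.2.1 alone would leave the conflict in place.

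The cost is a few sentences, a short eCRF entry for the baseline TMS procedures and one extra listing. The downside is a few more background stroke events to record in the days before session 1. The active-versus-sham comparison from session 1 onwards stays as planned.

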#### **9.2.2 Serious adverse events (SAEs)**

A serious adverse event is any untoward medical occurrence or effect that

- results in death;
- is life threatening (at the time of the event);
- requires hospitalization or prolongation of existing inpatients' hospitalization;
- results in persistent or significant disability or incapacity;

- is a congenital anomaly or birth defect; or
- any other important medical event that did not result in any of the outcomes listed above due to medical or surgical intervention but could have been based upon appropriate judgement by the investigator.

An elective hospital admission will not be considered as a serious adverse event.

The investigator will report all SAEs to the sponsor without undue delay after obtaining knowledge of the events, except for expected SAEs (see appendix B).

The sponsor will report all unexpected SAEs through the web portal *ToetsingOnline* to the accredited METC that approved the protocol, within 7 days of first knowledge for SAEs that result in death or are life threatening followed by a period of maximum of 8 days to complete the initial preliminary report. All other unexpected SAEs will be reported within 15 days after the sponsor has first knowledge of the serious adverse events.

Expected SAEs are events known to occur in patients with (subacute) stroke. Expected SAEs are defined in the protocol (Appendix B). Expected SAEs are excluded from expedited reporting but should be documented by the local investigator in the eCRF within 7 days of the investigator's first awareness about the event.

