## 5. TREATMENT OF SUBJECTS

### 5.1 Investigational treatment

#### Active cTBS

The intervention consists of 10 daily sessions of active or sham cTBS, delivered over the contralesional primary motor cortex (M1) in a period of 10 consecutive working days within a period of 17 days. The first cTBS session takes place within 21 days after stroke onset. cTBS treatment will be delivered prior to at least 40 minutes of regular care upper limb therapy, with a maximum time interval between cTBS and upper limb therapy of 15 minutes. Regular care upper limb therapy will be performed according to local protocols, which are based on national guidelines from the royal Dutch Society for Physical Therapy, and will be adjusted based on the patient's level of upper limb impairment. TMS procedures will be performed in accordance with recent safety guidelines for TMS.

Stimulation location is defined as the position on the scalp at which motor evoked potentials (MEPs) with the largest peak-to-peak amplitude could be evoked in the first dorsal interosseous (FDI) muscle of the unaffected arm by delivering TMS pulses and monitoring the electromyogram (EMG). Stimulation intensity is set at 70% of the resting motor threshold (RMT), which is defined as the minimum machine output at which stimulation evokes at least 5 of 10 MEPs with a peak-to-peak amplitude of over 50  $\mu$ V with the TMS coil oriented 45 degrees to the midline and an interstimulus interval of 7s. The stimulation location and intensity are determined before the 1st, 6th and 10th cTBS session.

cTBS consists of continuous delivery of bursts of 3 biphasic stimuli at 50 Hz repeated at 5 bursts per second for a duration of 40 seconds resulting in a total of 600 stimuli. During treatment, the TMS coil is placed on the scalp and oriented at 45 degrees to the midline.

Active cTBS will be delivered using an active figure-of-eight TMS coil.

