#### **6.4 Summary of known and potential risks and benefits**

Data from our phase II trial (B-STARS) shows that cTBS treatment leads to a clinically relevant improvement in upper limb recovery, with 17% (n 60; 9.6 points; 95%CI 1.2–17.9) additional recovery of upper limb activity, as measured with the ARAT score three months after stroke. This additional recovery led to a significant improvement in the activity and participation domain (of similar magnitude) of the International Classification of Functioning, Disability and Health (ICF) model, and a reduction in the length of stay at the rehabilitation center by 18 days on average. These findings corroborate results from a systematic review and meta-analysis of published studies, revealing benefit of rTMS on upper limb function if started within the first month after stroke.

The most serious adverse effect is the occurrence of a seizure at a crude risk of approximately 0.02% per stimulation session, as reported in a systematic review of 67 studies with 1,040 subjects and >4,500 sessions. More common adverse events during and after TBS are transient headache and neck pain, reported by <3% of subjects. CTBS treatment did not lead to seizures in our phase II trial. We only observed mild side effects, such as headache (<4%) and muscle pain (<1%) and the intervention was reported to be tolerable and comfortable.

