### **11.4 Benefits and risks assessment, group relatedness**

Data from our phase II trial (B-STARS) show that cTBS treatment leads to a clinically relevant improvement in upper limb recovery, with 17% (n 60; 9.6 points; 95%CI 1.2–17.9) additional recovery of upper limb activity, as measured with the ARAT three months after stroke. This additional recovery led to a significant improvement in activity and participation (of similar magnitude) and a reduction in the length of stay at the rehabilitation center by 18 days on average.

cTBS treatment only led to mild side effects, such as headache (<4%) and muscle pain (<1%) and was reported to be tolerable and comfortable. The risk of inducing an epileptic seizure is very small (0.02%) and consequences of an epileptic seizure can be mitigated by adequate training of personnel. The risk of experiencing an epileptic seizure in the early phase after stroke (not induced by TMS) varies from 2 to 12%. Therefore, rehabilitation centers have protocols in place. TMS-therapists are instructed to adhere to local protocols in case of an epileptic seizure. We are aware that including patients in a clinical trial in the early stages of recovery imposes a burden on them. However, evidence shows that treatment is most likely to be effective in the early post-stroke phase.

Therefore, cTBS treatment is likely to have a clinically relevant benefit, while the risk and burden of participation are negligible.

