| Cardiac
Angina
Arrhythmia
Atrial fibrillation
Angina pectoris
Bradycardia
Cardiac arrest
Cardiomyopathy
Heart failure
Myocardial infarction
Tachycardia                                                                                                                                             | Pulmonary
Aspiration
Bronchitis
Chronic obstructive pulmonary disease
Dyspnea
Obstructive sleep apnea
Oxygen desaturation
Pneumonia
Pulmonary embolism
Respiratory failure / arrest
Respiratory tract infection                                                                                                                    | Gastro-intestinal
Constipation
Dysphagia
Fecal incontinence
Gastro-intestinal hemorrhage
Ileus
Melena
Mucosal irritation
Nausea
Rectal hemorrhage
Stress ulcer
Vomiting |
| Central nervous system
Delirium
Depression
Epileptic seizure
Headache
Hydrocephalus
Recurrent ischemic stroke
Recurrent intracerebral hemorrhage
Recurrent stroke
Retinal ischemia
Sleep disorder
Status epilepticus
Spasticity
Transient ischemic attack
Transient monocular blindness | General / other
Anemia
Arterial hypertension
Arterial hypotension
Deep vein thrombosis
Dehydration
Fall (and consequences)
Fatigue
Fever
Hematuria
Hip fracture
Hyperglycemia
Infections
Pain
Pressure sore
Renal failure
Sepsis
Syncope
Undernutrition
Urinary incontinence
Urinary tract infection |                                                                                                                                                                                                                 |

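### The expected-SAE exemption in 9.2.2 covers epileptic seizure with no visible exception for a seizure linked to cTBS, and 11.4 and 13.2 drop the per-session unit from its risk

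*Combined protocol and SAP*

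**What the plan says.** Section 6.4 ranks the harm and gives its size: "The most serious adverse effect is the occurrence of a seizure at a crude risk of approximately 0.02% per stimulation session". The source is described as a review of "67 studies with 1,040 subjects and >4,500 sessions".

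Section 9.2.2 requires the investigator to report SAEs promptly to the sponsor, "except for expected SAEs (see appendix B". It explains the category by the underlying disease: "Expected SAEs are events known to occur in patients with (subacute) stroke". The consequence is also stated: "Expected SAEs are excluded from expedited reporting but should be documented by the local investigator in the eCRF within 7 days" of becoming aware of the event. Onward reporting to the ethics committee (METC) covers unexpected SAEs only.

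The expected-event table, which stands just before Appendix C, lists "Epileptic seizure" under the central nervous system and, further down the same cell, status epilepticus. Neither entry carries a condition.

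Section 9.2.3 sets a 24-hour route for serious adverse device effects. It requires that the event be unexpected, judged against the device's instructions for use (IFU).

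Section 11.4 reads "The risk of inducing an epileptic seizure is very small (0.02"; the bracket closes after the percent sign with no denominator. Section 13.2 does the same. Section 13.1j keeps the per-session unit.

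**The concern.** Whether an event is expected in stroke patients and whether it is a known harm of the stimulation are different questions. Section 9.2.2 asks only the first. Putting ordinary post-stroke seizures on an expected list is defensible. The difficulty is that the visible text makes no distinction for a seizure that starts under the coil or within hours of it. Such an event follows the same path as a listed background complication such as a urinary tract infection.

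At stake is how quickly the sponsor and DSMB are actively told of the harm that the protocol itself ranks highest. The missing unit matters less, but it bears on the benefit-risk argument. Section 11.4 places 0.02% in the same paragraph as a 2 to 12% risk of an early post-stroke seizure, which is a per-patient quantity, and then concludes that risk and burden are negligible. A reader will compare the two figures as if they had the same denominator.

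**Working it through.** **Reporting routes for a serious seizure shortly after a session**

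- Investigator to sponsor, prompt (9.2.2): not required, because the event is on the expected list.
- Sponsor to METC, 7 or 15 days (9.2.2): not required, because this covers unexpected SAEs only.
- Device-effect route, 24 hours (9.2.3): open only if the seizure's nature or severity departs from the IFU. If the IFU names seizure, the route is probably closed. Section 6.1 lists five stimulators, so the same seizure could be classified differently between centres if their IFUs differ.
- SUSAR route and annual safety report (9.2.4, 9.3): marked not applicable.
- eCRF entry within 7 days (9.2.2): applies.
- DSMB (9.5): receives SAE listings and meets at least annually. No trigger or deadline specific to seizures is stated.

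The only prompt route that might remain therefore depends on a source outside the documents.

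**Size of the risk**

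Inputs: 0.02% per session, and more than 4,500 sessions in 1,040 subjects (6.4); 10 sessions per patient (5.1: "The intervention consists of 10 daily sessions of active or sham cTBS"); 454 patients (4.4) at 1:1 (SAP section 2), so 227 on active cTBS.

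1. *The plan's own figure.* The seizure count is not given. With one seizure assumed, 1/4,500 = 0.022%, which rounds to the stated 0.02%. Two would give 0.044%, which does not fit. The per-session figure is reproduced.
2. *Per participant.* With constant, independent session risk p, the risk over 10 sessions is 1 − (1 − p)^10. With p = 0.0002 this is 0.1998%, about 1 in 500, or 9.99 times the figure printed without a unit.
3. *Range.* If 0.02% is a rounding of 0.015% to 0.025%, the result is 0.15% to 0.25%. Eight sessions give 0.16%. The unrounded 1/4,500 gives 0.22%.
4. *Active arm.* 227 × 10 = 2,270 sessions; 2,270 × 0.0002 = 0.454 expected induced seizures; 1 − (1 − 0.0002)^2,270 = 36.5% chance of at least one. If 0.02% is misread as per patient: 227 × 0.0002 = 0.045 expected and a 4.4% chance.
5. *Sampling uncertainty.* If the source is one seizure in 4,500 sessions, the exact 95% interval per session is 0.0006% to 0.124%. The upper limit gives 2,270 × 0.00124 = 2.8 expected seizures, and the lower limit about 0.01. The 0.45 is a central value with wide limits.

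**The case against.** The strongest reply is that the plan has more safeguards than 9.2.2 suggests, and much of that reply stands.

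- *A reader might infer that no prompt route exists.* The documents do not show this. The 24-hour route in 9.2.3 judges expectedness against the IFU, not against the expected list, so listing a seizure does not close it. Whether it is open cannot be settled without the IFU.
- *A reader might infer that the sponsor and DSMB would learn of an induced seizure only at an annual meeting or at the 150-patient look.* That does not follow. The eCRF entry is due within 7 days, and section 12.1 gives the coordinating investigators access to the combined CASTOR dataset. Annual is the minimum DSMB frequency, and the 150- and 300-patient analyses come in addition to the listings. What is missing is active notification, not access.
- *A reader might infer that induced seizures would be hidden by the 2 to 12% background.* The trial is randomised and sham-controlled, so background seizures fall in both arms. SAP 7.8 tabulates events by arm, and section 8.3 records the date and time of every session. It is fair to say only that, with fewer than one induced seizure expected, a count by arm says little and time since the last session says more.
- *A reader might infer that the protocol misstates the risk tenfold.* It prints no per-patient figure, and 6.4 and 13.1j give the unit correctly. Two sections omit it.
- *The 36% concerns induced seizures of any severity.* Only those meeting the SAE criteria fall under the exemption, and the documents do not give that share.

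One further caution: the heading of the expected-event table and any text introducing it are not in the text available to me. A qualifier could sit there. The full Appendix B should be checked first.

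**Conclusion.** The point holds as a gap in safety-reporting wording. On the visible text, a serious seizure or status epilepticus during or shortly after cTBS is exempt from prompt reporting to the sponsor and from expedited reporting, with eCRF entry within 7 days remaining, unless the IFU-dependent route in 9.2.3 applies. This sits badly with 6.4. The conclusion assumes that Appendix B has no qualifying introduction. It does not support a claim that such an event would stay unseen for a year or more.

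The unit point is real but smaller. The figure of about 0.2% per participant is derived, not printed. It assumes constant and independent session risk, and that a rate from a mixed review population carries over to these patients. Neither part affects the efficacy analysis. The change is worth making because it is cheap and concerns the harm that the protocol ranks first.

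**What to change.** Reconcile 6.4, 9.2.2, 9.2.3 and Appendix B:

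- In 9.2.2, state that the expected-SAE exemption does not cover a serious seizure or status epilepticus that is judged possibly related to cTBS or occurs soon after a session. The sponsor sets the window. One candidate is 24 hours, the duration of side effects given in 9.2.1. There it justifies the 3-week recording period and is not itself a reporting rule.
- State that these events go to the sponsor without undue delay and are forwarded to the DSMB.
- In SAP 7.8, add a listing of seizures by arm with time since the last session. The session times are already collected under 8.3.
- In 11.4 and 13.2, restore the per-session unit and add that it corresponds to about 0.2% per participant over 10 sessions, with the assumption stated.

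The cost is protocol and SAP wording plus a few extra expedited reports. Their number cannot be derived exactly from the documents: about 0.45 induced seizures of any severity are expected, plus whatever serious background post-stroke seizures happen to fall inside the window. Some reports will therefore concern events that cTBS did not cause.
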